## Abstract

**Background:**

Diarrhea is one of the leading causes of death, killing 1.3 million in 2013 across the globe, of whom, 0.59 million were children under 5 years of age. Globally, about 1 billion people practice open defecation, and an estimated 2.4 billion people were living without improved sanitation facilities in 2015. Much of the previous research investigating the effect of improved sanitation has been based on observational studies. Recent studies have executed a cluster-randomized controlled trial to investigate the effect of improved sanitation. However, none of these recent studies achieved a sufficient level of latrine coverage. Without universal or at least a sufficient level of latrine coverage, a determination of the effect of improved latrines on the prevention of diarrheal disease is difficult.

This cluster-randomized trial aims to explore the net effect of improved latrines on diarrheal prevalence and incidence in children under five and to investigate the effect on the diarrheal duration.

**Method/design:**

A phase-in and factorial design will be used for the study. The intervention for improving latrines will be implemented in an intervention arm during the first phase, and the comparable intervention will be performed in the control arm during the second phase. During the second phase, a water pipe will be connected to the *gotts* (villages) in the intervention arm. After the second phase is completed, the control group will undergo the intervention of receiving a water pipe connection. For diarrheal prevalence, five rounds of surveying will be conducted at the household level. The first four rounds will be carried out in the first phase to explore the effect of improved latrines, and the last one, in the second phase to examine the combined effects of improved water and sanitation. For documentation of diarrheal incidence and duration, the mother or caregiver will record the diarrheal episodes of her youngest child on the “Sanitation Calendar” every day. Of 212 *gotts* in the project area, 48 *gotts* were selected for the trial, and 1200 households with a child under 5 will be registered for the intervention or control arm. Informed consent from 1200 households will be obtained from the mother or caregiver in written form.

**Discussion:**

To our knowledge, this is the second study to assess the effects of improved latrines on child diarrheal reduction through the application of Community-Led Total Sanitation.

**Trial registration:**

Current Controlled Trials, ISRCTN82492848

## Background

Diarrhea is one of the leading causes of death, killing 1.3 million in 2013, of whom 0.59 million were children under 5 years of age [1]. This preventable and curable disease accounts for 11 % of child mortality [2]. The lack of improved sanitation is the most important contributing factor to diarrheal disease in many low-income countries [3].

During the Millennium Campaign period, sanitation coverage has not progressed as planned and remains a daunting challenge for the next campaign of the Sustainable Development Goals [4, 5].

Globally, approximately 1 billion people practice open defecation, and an estimated 2.4 billion people lived without improved sanitation facilities in 2015 [1]. Sub-Saharan Africa showed slower progress in sanitation coverage, reaching 31 % in 2015 from 24 % in 1990, whereas South Asia has increased coverage to 49 % from 22 % in the same period [1].

Inequality in coverage also exists between rural and urban areas. In contrast with 40 % of the urban population accessing improved sanitation in sub-Saharan countries, only 23 % of people in rural areas have access to improved sanitation [1].

Ethiopia shows a high child mortality rate, with 74.4 children out of 1,000 live births dying before they reached the age of five in 2013. Diarrheal disease accounts for 9 % of child mortality, ranking as the fourth most frequent cause of child deaths [6]. In Ethiopia, 72 % of the people are living without improved sanitation facilities [7].

Much of the previous research investigating the effect of improved sanitation has been based on observational studies [8–11]. According to the results of a recent systematic review [12], few studies have involved a cluster-randomized controlled trial on sanitation intervention. Recently, several studies [13–15] have investigated the effect of improved sanitation, executing a cluster-randomized controlled trial. These studies did not demonstrate any protective effect of improved latrines against child diarrheal prevalence. However, none of the recent studies achieved universal or even a sufficient level of coverage required for fostering herd immunity. Without universal or at least a sufficient level of latrine coverage, the effect of improved latrines on the prevention of diarrheal disease is difficult to determine. Furthermore, most of the recent studies employing rigorous methodology have been conducted in South Asia. Since a number of people are living without improved sanitation in sub-Saharan Africa, a strong need exists for further evidence of the effect of improved sanitation in rural sub-Saharan Africa.

This study aims to explore the net effect of improved latrines on reducing diarrhea in children under five, particularly when latrine coverage reaches a certain threshold level. In addition, we aim to investigate the effect of improved latrines on the diarrheal duration of children by recording diarrheal incidence on a daily basis.

This study was designed as a cluster-randomized trial in the Southern Nations, Nationalities, and Peoples’ Region (the SNNPR State), Ethiopia, with the aim of finding evidence of the effect of improved latrines on diarrheal diseases in children under five. To our knowledge, this is the second study to assess the effects of improved latrines on child diarrheal reduction through the application of Community-Led Total Sanitation.

## Methods/design

### Study setting

The Cheha District and Enemore Ena Ener District, the target area of the project, are located 185 km southwest of Addis Ababa. According to the District Statistics Office, the total population of each district was 133,233 and 204,937, respectively, in 2014. Both districts are predominantly rural areas with 90 % of the entire land used for farming, and the major sources of income are crop production and livestock farming. Coffee, *chat*, and oil seeds are among the major cash crops in both districts, and plantations of eucalyptus trees for income are also very common. The dominant ethnic group, which accounts for more than 80 % of the population in the area, is the Gurage people, after which the administrative zone of the area is named (Gurage Zone). Of the population in the area, 64 % are Muslim, whereas 33 % identified themselves as Ethiopian Orthodox Christian (Fig. 1).

**Fig. 1 Fig1:**
[figure not shown]
Project area and study area

### Study design

The study was approved by the National Research Ethics Review Committee under the Ministry of Science and Technology, Federal Democratic Republic of Ethiopia (NRERC 3.10/032/2015; July 29, 2015) and was registered as an ISRCT on March 13, 2015 (ISRCTN82492848).

In the study, a *gott*, the Amharic word for village, was taken as the randomization unit because we expected that improved latrines could impact diarrheal transmission across households within a *gott*, where people interact with one another most closely. All the interventions related to latrine improvement will be performed at each *gott* level.

A phase-in and factorial design will be used for the study. The intervention for improving latrines will be implemented in the intervention arm during the first phase, and the comparable intervention will be performed in the control arm during the second phase. During the second phase, a water pipe will be connected to the *gotts* in the intervention arm. After the second phase is completed, the control group will receive the intervention of a water pipe connection. With the design, we will investigate not only the effect of improved sanitation but also the combined effects of improved water and sanitation interventions.

A preliminary survey was carried out to develop this water, sanitation, and hygiene (WaSH) project intervention design in March to May 2013. Water pipes will be connected to 212 *gotts*, of which, 48 *gotts* were selected as the study area of the trial. In the intervention *gotts*, the procedures of the Community-Led Total Sanitation including pre-triggering, triggering, and follow-up will be carried out for latrine improvement beginning in November 2015 and will continue to October 2016.

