### Primary endpoint

The primary endpoint of the study is diarrheal prevalence in children under 5 years of age. We will use 7-day prevalence of reported diarrhea in the household, which will be based on parental reports. The survey will be conducted five times at the household level: the first four rounds will be carried out in the first phase to explore the effect of improved latrines, and the last one, in the second phase to assess the combined effects of improved water and sanitation.

In addition to diarrheal prevalence, we will measure diarrheal incidence and diarrheal duration. For documentation of diarrheal incidence and duration, we will have the mother or caregiver record the diarrheal episodes of her youngest child on a “Sanitation Calendar” (Amharic language: *Yenezehenna Gize Saleda*) on a daily basis (Fig. 2).

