### Water intervention

When the CLTS intervention is completed, the second phase starts, during which water pipes will be connected to 24 *gotts* from one single spring on a mountain in each district. A spring capable of supplying sufficient water across the district is already identified and designing a water-pipe connection plan is under process. Immediately after the final round of the survey is finished, the water pipe will be connected to all the other 24 *gotts*.

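### Round 5 is said to assess the combined effect of water and latrines in a factorial design, but its randomised contrast is latrines plus water against later-started latrines

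*Protocol article*

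**What the plan says.** The abstract (Method/design) and the Study design section both name the design: "A phase-in and factorial design will be used for the study". Study design adds what it is meant to deliver: "With the design, we will investigate not only the effect of improved sanitation but also the combined effects of improved water and sanitation interventions". Primary endpoint allots the surveys: four rounds in the first phase for latrines, and "the last one, in the second phase to assess the combined effects of improved water and sanitation".

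The same sections fix who receives what. The intervention arm has the latrine programme in phase 1, "and the comparable intervention will be performed in the control arm during the second phase". For piped water in the intervention villages: "During the second phase, a water pipe will be connected to the" intervention arm. For the control villages: "After the second phase is completed, the control group will receive the intervention of a water pipe connection". Water intervention ties this to the surveys: "Immediately after the final round of the survey is finished, the water pipe will be connected to all the other 24" villages. The Sanitary survey section dates the fifth round to July 2017. It is the only round in phase 2.

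**The concern.** A combined effect of water and sanitation is the difference between having both and having neither. A factorial design would provide it because it allocates the two components separately, giving four groups: neither, latrines, water, both. Here water follows the latrine allocation, and the control arm is given latrines in the same phase in which the intervention arm is given water. The arm that should represent neither component at round 5 is not assigned to that state.

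If the round-5 difference were reported under the label the article gives it, an estimate of one quantity would be published as another. Provided the control arm's latrines do some good, the error runs in one direction: the combined effect is understated. Nor is the difference a pure water effect, because the intervention arm has also had latrines for longer.

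**Working it through.** **The plan's own figure.** The article gives no figure for round 5 or for the combined effect. Its prevalence sample size assumes one contrast: 24 % reduced by 30 %, that is 0.24 × 0.70 = 0.168. The standard formula for unmatched clusters, with 25 children per village, k = 0.15, 80 % power and two-sided 5 % (assumed; the article does not state it for prevalence), gives

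c = 1 + (1.960 + 0.842)² × [(0.24×0.76 + 0.168×0.832)/25 + 0.15²(0.24² + 0.168²)] / 0.072² = 23.44.

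That is 24 villages and 24 × 25 = 600 children per arm, as stated. The latrine risk ratio (RR) of 0.70 is thus the article's own planning value, and it is used below.

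**Step 1: what each arm receives.**

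| | Intervention arm (24) | Control arm (24) | Contrast |
|---|---|---|---|
| Phase 1, rounds 2–4 | latrines | neither | latrines vs none |
| Phase 2, round 5 | latrines since phase 1, plus water | latrines started in phase 2 | latrines + water vs later latrines |
| After the final round | latrines + water | latrines + water | no survey |

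Of the four factorial groups, water alone is never observed, and no arm is assigned to neither component in phase 2.

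**Step 2: the estimand.** On the log scale let S be the latrine effect, W the water effect, I their interaction, and f the share of S that the control arm has reached by July 2017.

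- Combined effect: S + W + I
- Phase 1 contrast: S
- Round-5 contrast: S + W + I − f·S

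The round-5 contrast equals the combined effect only at f = 0. At f = 1 it is W + I, water added to latrines. In between, it mixes water with the difference in latrine exposure.

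**Step 3: dates.** The phase 1 latrine work runs from November 2015 to October 2016, and phase 2 follows it. July 2017 is about 9 months after October 2016. If control latrine work starts when phase 2 does, it is well under way by round 5. The article itself surveys for a latrine effect in March and July 2016, about 4 and 8 months after the phase 1 start. So f = 0 is not what its own schedule anticipates, but f = 1 is not established either.

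**Step 4: size.** Assumptions: latrine RR 0.70 (article); water RR 0.80 (not in the article); multiplicative effects (I = 0). The combined RR is 0.70 × 0.80 = 0.56, a 44 % reduction. Round-5 RR = 0.56 / 0.70^f:

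| f | Round-5 RR | Reduction shown | True combined reduction |
|---|---|---|---|
| 0 | 0.56 | 44 % | 44 % |
| 0.5 | 0.56/√0.70 = 0.67 | 33 % | 44 % |
| 1 | 0.56/0.70 = 0.80 | 20 % | 44 % |

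For a water RR from 0.70 to 0.90, the combined reduction runs from 51 % to 37 %. Round 5 shows 30 % to 10 % at f = 1, and 41 % to 25 % at f = 0.5. If water does nothing (RR 1.00) and f = 0.5, round 5 still shows 0.70/√0.70 = 0.84, a 16 % reduction due to latrine exposure alone.

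**Step 5: chaining.** Adding the phase 1 and round-5 contrasts gives S + W + I + (1 − f)·S. This is the combined effect exactly at f = 1: 0.70 × 0.80 = 0.56. At f = 0.5 it gives 0.70 × 0.67 = 0.47, a 53 % reduction, which is too large. With a stable latrine effect and f between 0 and 1, the round-5 contrast and the chained estimate therefore lie on either side of the combined effect.

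**The case against.** The strongest reply is that this concerns a supplementary contrast. The aims in the abstract and Background are the effect of improved latrines on diarrhoea and on its duration, and the Discussion concludes only about latrines. The combined effect appears in the design and survey descriptions and is attached to one round of five. The sanitation calendar ends in November 2016, so on the stated dates incidence and duration have no phase-2 data. All of this stands. A reader might infer that one of the trial's two stated questions is unanswerable; the stated aims do not support that.

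A reader might also infer that both arms will have completed the latrine programme by round 5, and so take 20 % against 44 % as the expected error. The article places the control programme in phase 2 without dating its completion. Phase 1 took about 12 months and round 5 falls about 9 months after it ends, so the control work may still be under way. The 20 % is the full-effect case, not the result.

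A third tempting reading is that no randomised evidence bears on the combined effect. That is too strong. No single contrast estimates it, but two randomised contrasts in the same villages can be chained if the latrine effect is stable and the control effect is realised.

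Finally, the Data analysis section names no contrast for the combined effect, and an analysis plan may exist. Nothing shows that the raw round-5 difference will be reported under that label. This makes the harm conditional, but it does not repair the text: the article states a design type and a purpose for round 5 that its own schedule contradicts, and no later plan can supply a randomised arm with neither component.

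**Conclusion.** The point holds as a wrong design label and a wrong estimand for round 5. The trial has two phased arms and is not factorial. Round 5 is a valid randomised comparison and is informative, but about water added to latrines together with any difference in latrine exposure time. It would equal the combined effect only if the control arm's latrine work had no effect by July 2017.

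Under the article's latrine RR of 0.70, an assumed water RR of 0.80 and multiplicative effects, a combined reduction of 44 % would appear as 20 % with the control latrine effect fully realised and about 33 % with it half realised on the log scale. The direction needs only that the control latrines have some benefit; the size depends on the assumed water effect and on f, neither of which the article gives. The phase 1 latrine comparison, the main aim, is unaffected.

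**What to change.** - Remove the factorial label from the abstract and Study design, and describe a two-arm phased design.
- In Study design and Primary endpoint, define the round-5 estimand as the effect of adding piped water to the latrine intervention, and state that it includes any difference in latrine exposure time between the arms. Report how far the control arm's latrine work had progressed at round 5; the monthly sanitation maps planned for all 48 villages can supply this.
- Do not report the round-5 difference as the combined effect.
- If a combined effect is wanted, chain the phase 1 contrast (latrines vs none) with the round-5 contrast, and state the assumptions: a latrine effect stable over time and a control latrine effect realised by round 5. Show the result beside the round-5 contrast, since the two err in opposite directions when the control effect is only partly realised.
- A comparison across years, such as control July 2016 against intervention July 2017, matches season but not age, because the cohort is closed and the children are a year older. Present it, if at all, as a labelled non-randomised, age-adjusted, supportive analysis.

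The cost is wording and a little analysis, with no change to field work. The price is a narrower claim for round 5.

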### Primary endpoint

The primary endpoint of the study is diarrheal prevalence in children under 5 years of age. We will use 7-day prevalence of reported diarrhea in the household, which will be based on parental reports. The survey will be conducted five times at the household level: the first four rounds will be carried out in the first phase to explore the effect of improved latrines, and the last one, in the second phase to assess the combined effects of improved water and sanitation.

In addition to diarrheal prevalence, we will measure diarrheal incidence and diarrheal duration. For documentation of diarrheal incidence and duration, we will have the mother or caregiver record the diarrheal episodes of her youngest child on a “Sanitation Calendar” (Amharic language: *Yenezehenna Gize Saleda*) on a daily basis (Fig. 2).

**Fig. 2 Fig2:**
[figure not shown]
Sanitation calendar

### Sample size calculation

#### Period prevalence of diarrhea

The prevalence of diarrhea was estimated to be 24 % on the basis of a preliminary survey in the SNNPR State, and we expect that our intervention will lead to a 30 % relative reduction on the basis of systematic review results [16]. Assuming a design effect of 2.14 and a coefficient of variation of 0.15, an 80 % study power resulted in 48 clusters (48 *gotts*) and 600 children per arm. We employed a two-stage cluster-sampling method for the study. Among the 212 *gotts* targeted by the project for the water pipe connection, 48 *gotts* were chosen as primary sampling units.

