#### Incidence density of diarrhea in terms of child-weeks

The expected value of the incidence density, E (*s*^2^), is given by$$ \mathrm{E}\left({\mathrm{s}}^2\right) = \lambda \mathrm{A}\mathrm{v}\left(1/{\mathrm{y}}_{\mathrm{j}}\right) + {\sigma^2}_{\mathrm{c}}=\lambda \mathrm{A}\mathrm{v}\left(1/{\mathrm{y}}_{\mathrm{j}}\right) + {\mathrm{k}}^2{\lambda}^2, $$

where λ is the true mean rate, *y*_*j*_ corresponds to the child-weeks of follow-up in the *j*^th^ cluster, Av() indicates the mean overall clusters, *σ*_*c*_^2^ is the between-cluster variance of the true rates, and *k* is the coefficient of variation of those rates [17]. Based on the preliminary survey, the overall diarrheal rate in the 48 *gotts* was 0.18 (or 18 cases per 100 child-weeks). The empirical standard deviation of the observed diarrhea rates was 0.092189, and the average of the reciprocal child-weeks per neighborhood was 0.001667. Therefore, *k* was estimated as$$ \begin{array}{c}\hfill {\sigma}^2={0.092189}^2-0.18\times 0.001667=0.008199,\hfill \\ {}\hfill \hfill \\ {}\hfill \mathrm{and}\;\mathrm{therefore},\;k=\surd \left(0.008199/0.18\right)=0.213422.\hfill \end{array} $$

We assumed that the diarrhea rate in the control *gotts* remained constant at λ_0_ = 0.18, and we required 90 % power (*z*_*β*_ = 1.28) if the intervention reduced the diarrhea rate by 21 %. Assuming 600 child-weeks of observation (24 weeks of follow-up for 25 children) in each *gott*, the number of neighborhoods required for each treatment group is given by c = 1 + (1.96 + 0.28)^2^[(0.18 + 0.1422)/600 + 0. 213422^2^(0. 18^2^ + 0. 1422^2^)]/(0.18 − 0.1422)^2^ = 22.55.

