### Household sampling methods

A list of households with children under 5 years of age was established by four supervisors in each *gott* before the baseline survey. Supervisors required 8 days to produce a complete household list for all 48 *gotts*. Using SPSS 21 Statistics software, the survey team leader randomly sampled 25 households from each *gott*. Enumerators will recruit the youngest child under five from each household, from the fifth week of October through the second week of November 2015. If the mother or a household caregiver is absent at the time of the recruitment visit, the enumerator will revisit the same household two more times. If the mother or caregiver refused to be registered, a neighboring household with a child under 5 was visited to replace the household (Fig. 3).

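### The primary-endpoint sample size cites two clustering inputs (design effect 2.14, CV 0.15) that disagree under the usual definitions; only CV 0.15 yields the stated 600 children per arm at 80 % power

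*Protocol article*

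**What the plan says.** All inputs are in the protocol article, under Sample size calculation, Period prevalence of diarrhea, unless noted.

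- Control prevalence: "The prevalence of diarrhea was estimated to be 24" %.
- Effect: "we expect that our intervention will lead to a 30 % relative reduction", so 24 % against 16.8 %.
- Clustering: "Assuming a design effect of 2.14 and a coefficient of variation of 0.15". The paragraph gives no intracluster correlation, no source for either value, and no account of how the two were combined.
- Result: "an 80 % study power resulted in 48 clusters (48 *gotts*) and 600 children per arm".
- Cluster size, from Household sampling methods: "the survey team leader randomly sampled 25 households from each" gott. CLTS implementation puts 24 of the 48 gotts in the intervention arm, so each arm has 24 gotts of 25.
- Meaning of the coefficient of variation: the prevalence paragraph does not define it. The next subsection, on incidence density, introduces k for cluster rates and says that it "is the coefficient of variation of those rates".

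**The concern.** For a binary outcome with a fixed number of children per gott, the design effect and the between-gott coefficient of variation are two expressions of the same between-gott variance. Once prevalence and cluster size are set, one determines the other. The two values quoted together here are far apart on that conversion, so at most one of them can lie behind the stated sample size.

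What is at stake is the stated 80 % power for the primary endpoint. A reader who takes the design effect at face value and divides 600 by it does not arrive at 80 %. The document gives no way to tell which of the two values reflects what the authors believe about variation between gotts.

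**Working it through.** **Inputs.** p1 = 0.24, p2 = 0.24 x 0.70 = 0.168, difference 0.072, m = 25 per gott, 24 gotts (600 children) per arm, power 80 %. The prevalence paragraph states no significance level. I assume two-sided 0.05, in line with the 1.96 in the incidence formula.

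Variance sum: 0.24 x 0.76 + 0.168 x 0.832 = 0.1824 + 0.1398 = 0.3222.

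**Step 1: reproduce the plan's figure from the CV.** Cluster formula for proportions:

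c = 1 + (1.96 + 0.8416)² x [0.3222/25 + k²(p1² + p2²)] / 0.072²

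With k = 0.15: c = 1 + 7.849 x [0.01289 + 0.0225 x 0.08582] / 0.005184 = 23.4, so 24 gotts per arm. That is 48 in total and 600 children per arm, as stated. Power with c = 24 is Φ(√(23 x 0.005184/0.01482) − 1.96) = Φ(0.877) = 81 %. The design effect is not needed anywhere.

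**Step 2: try the design effect instead.** Individually randomised size: n = 7.849 x 0.3222/0.005184 = 488 per arm. Times 2.14 = 1,044 per arm, or 1,044/25 = 41.8, so 42 gotts. The pooled-variance version gives 491 x 2.14 = 1,051. Neither is 600. Conversely, 600/488 = 1.23 is about the largest design effect that 600 per arm can carry at 80 % power.

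**Step 3: convert one input into the other.** ρ = k²p/(1 − p) and DE = 1 + (m − 1)ρ, at p = 0.24.

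| Stated input | ρ | Design effect | CV |
|---|---|---|---|
| CV 0.15 | 0.0225 x 0.24/0.76 = 0.0071 | 1 + 24 x 0.0071 = 1.17 | 0.15 |
| Design effect 2.14 | 1.14/24 = 0.0475 | 2.14 | √(0.0475 x 0.76/0.24) = 0.39 |

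At p = 0.168 the gap is wider: CV 0.15 gives a design effect of 1.11, and 2.14 gives a CV of 0.49.

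**Step 4: a possible origin.** If 0.15 is entered without squaring, DE = 1 + 24 x 0.15 x 0.24/0.76 = 2.137, which rounds to 2.14. So either a square was dropped when the design effect was computed, or 0.15 is really the squared CV. The first leaves the sample size intact; the second does not. The match may also be chance, and the document does not settle it.

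**Step 5: power if 2.14 is the intended value.** Effective size 600/2.14 = 280 per arm. Standard error √(0.3222/280.4) = 0.0339. Power = Φ(0.072/0.0339 − 1.96) = Φ(0.164) = 56.5 %, about 57 %. Variants:

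- pooled variance: 56.2 %
- t-test on 46 df: about 55 %
- cluster formula at CV 0.39: 57.5 %
- one-sided 0.05: 68 %

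The relative reduction detectable with 80 % power is 38.9 %, about 39 %.

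**The case against.** **The stated power is not miscalculated.** This is the strongest reply, and it stands. CV 0.15 is in the text and leads to the stated gotts, children and power. A reader might infer that the trial's true power is 57 %. The document does not support that: the figure applies only if 2.14 is the intended value, and nothing says that it is.

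**The CV may mean something else.** The prevalence paragraph does not define it. It could be the CV of gott size, or a within-kebelle CV set beside an overall design effect, since allocation is stratified by kebelle. The two inputs could then coexist, so it is too strong to say that they can never both hold. But the incidence subsection's definition and the exact reproduction in Step 1 both favour the between-gott reading. Reading 0.15 as size variation does not rescue 80 % either: 2.14 still leaves about 56 %, and any further inflation (to about 2.17) lowers it.

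**48 clusters might be per arm.** With 1,200 children per arm, power at 2.14 would be about 85 %. The stated 600 per arm, 1,200 households and 24 intervention gotts rule this out.

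**Repeated rounds add power.** They do, and one might wrongly conclude that they cannot make up the shortfall. In a beta-binomial simulation with ICC 0.0475 and a gott effect that persists fully over time, power is about 59 % for one round unadjusted, 71 % for one round adjusted for baseline, 76 % for three follow-up rounds unadjusted, and 93 % for three rounds adjusted for baseline. Full persistence is optimistic. More to the point, the prevalence paragraph does not use the repeated rounds, and Data analysis mentions neither baseline nor kebelle adjustment. The rounds therefore soften the likely consequence without explaining the stated figure.

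**The incidence section's k of 0.21.** A reader might count this as a third conflicting value. It describes a different outcome, a rate per child-week, and need not equal the CV for a 7-day prevalence.

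**Conclusion.** The point holds as an unreconciled pair of inputs behind the primary endpoint's power. On the between-gott reading, CV 0.15 means a design effect of about 1.17 and supports the stated 24 x 25 per arm at about 81 % power. The design effect of 2.14 means a CV of about 0.39, would need about 1,044 children per arm, and appears not to have entered the calculation.

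The loss of power is conditional. If 2.14 is the intended value, power is about 57 % and the detectable reduction about 39 %. This rests on two-sided 0.05, 25 children in every gott, and a single-round unadjusted comparison of 24 % with 16.8 %. If CV 0.15 is intended and can be sourced, the sample size stands and only the 2.14 is wrong.

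**What to change.** In the prevalence paragraph:

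1. Say which clustering assumption applies to 7-day prevalence, define it, and give its source.
2. Correct or delete the other. If CV 0.15 is kept, the matching design effect is about 1.17. If 2.14 is kept, the matching CV is about 0.39.
3. Restate power for the fixed 24 gotts of 25 per arm, with the significance level. Say whether the figure refers to one round or to repeated rounds, and with or without baseline adjustment.

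The incidence endpoint may keep its own CV. The cost is one reworded paragraph and possibly a less favourable stated power. No recruitment is added.

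### The primary-endpoint sample size pairs a design effect of 2.14 with a coefficient of variation of 0.15; the two conflict, and 2.14 gives about 57 % power at 600 per arm, not 80 %

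*Protocol article*

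**What the plan says.** The protocol article's section on period prevalence of diarrhea, under Sample size calculation, sets out the power for the primary endpoint. For the control arm: "The prevalence of diarrhea was estimated to be 24" per cent. For the effect: "we expect that our intervention will lead to a 30 % relative reduction", so 16.8 % in the intervention arm. It continues: "Assuming a design effect of 2.14 and a coefficient of variation of 0.15", and reports that "an 80 % study power resulted in 48 clusters" "and 600 children per arm".

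The cluster size comes from Household sampling methods, where "the survey team leader randomly sampled 25 households from each" gott and one child per household is recruited. CLTS implementation assigns 24 of the 48 gotts to the intervention arm, and the abstract gives 1200 households in all. The design is therefore 24 gotts of 25 children, 600 children, in each arm.

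The prevalence section does not define its coefficient of variation. The next section, on incidence density, defines the between-cluster quantity k, which "is the coefficient of variation of those rates".

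**The concern.** A design effect and a between-cluster coefficient of variation are two ways of expressing the same thing. Once prevalence and cluster size are fixed, one determines the other. The protocol gives both as joint assumptions, and they look far apart: 2.14 more than doubles the required sample, whereas 0.15 is mild clustering for groups of 25. There is also a simpler check. If 600 per arm already includes a factor of 2.14, only about 280 per arm would have been needed under individual randomisation, which looks too few for 24 % versus 16.8 %.

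At stake is the power claim for the primary endpoint. A reader is told that 80 % power was kept after a generous clustering allowance. If 2.14 is the investigators' real expectation, the stated power is wrong by more than 20 percentage points. If 0.15 is, the allowance was about 17 %, not 114 %. The Background section stresses that recent trials found no protective effect, so how a null result here would be read depends on this figure.

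**Working it through.** **Inputs.** p0 = 0.24 and p1 = 0.24 × 0.70 = 0.168, difference 0.072; 80 % power; design effect 2.14; coefficient of variation k = 0.15; 600 children per arm (all from the prevalence section). m = 25 per gott (Household sampling methods). 24 gotts per arm (CLTS implementation). The prevalence section does not state alpha. I assume two-sided 5 %, because the incidence calculation uses 1.96, and give one-sided results as well.

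Sum of binomial variances: 0.24 × 0.76 + 0.168 × 0.832 = 0.3222. (1.96 + 0.8416)² = 7.849.

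**1. Reproducing the printed size from k = 0.15.** The cluster formula has the same form as the one printed for incidence:

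c = 1 + 7.849 × [0.3222/25 + 0.15² × (0.24² + 0.168²)] / 0.072²
= 1 + 7.849 × [0.012887 + 0.001931] / 0.005184 = 23.4.

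Rounded up, this is 24 gotts and 600 children per arm, as printed. Power with 24 gotts, allowing for the added 1, is Φ(√(23 × 0.005184/0.014818) − 1.96) = Φ(0.88) = 81 %.

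**2. Trying to reproduce it from the design effect of 2.14.**

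- Individually randomised n = 7.849 × 0.3222 / 0.005184 = 488 per arm (491 with pooled variance, 518 with continuity correction).
- 487.8 × 2.14 = 1,044 per arm, and 1,044/25 = 41.8, so 42 gotts per arm. The variants give 1,051 and 1,109. One-sided 5 % still needs about 822 to 886.
- The largest design effect that 600 per arm can carry at 80 % power is 600/488 = 1.23.

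**3. Power at 600 per arm if 2.14 holds.**

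- Effective n = 600/2.14 = 280.4.
- z = 0.072/√(0.3222/280.4) = 2.124, so power = Φ(2.124 − 1.96) = Φ(0.164) = 56.5 %.
- Pooled variance gives 56.2 %. The cluster formula with the equivalent k of 0.388 gives 57.5 %. One-sided 5 % gives 68 %.
- At 80 % power, two-sided, the detectable relative reduction is about 39 %.

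**4. Converting one clustering figure into the other.** ICC = k²p/(1 − p), and design effect = 1 + (m − 1) × ICC.

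| Starting from | ICC at p = 0.24 | Design effect, m = 25 | k |
|---|---|---|---|
| k = 0.15 | 0.0225 × 0.24/0.76 = 0.0071 | 1 + 24 × 0.0071 = 1.17 | 0.15 |
| Design effect 2.14 | 1.14/24 = 0.0475 | 2.14 | √(0.0475 × 0.76/0.24) = 0.39 |

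For k = 0.15 to yield 2.14, each gott would need 1 + 1.14/0.0071 ≈ 161 children.

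Steps 2 and 3 do not use the conversion in step 4, so the conflict between 2.14 and the stated power does not depend on how the coefficient of variation is read.

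**The case against.** The best defence is that the printed result is right under one of its two stated inputs: k = 0.15 gives 24 gotts per arm and just over 80 % power. On that view the design effect is a stray figure, and 57 % is not the trial's power but what follows if 2.14 is true. This stands as a matter of framing: 57 % is conditional. It does not rescue the sentence, which presents both figures as assumptions behind the size.

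Other points:

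- **Was 2.14 used at all?** The arithmetic cannot settle this. A single-prevalence precision calculation with a margin of ±5 points gives 1.96² × 0.24 × 0.76/0.05² × 2.14 = 599.8, very close to 600. That margin is an assumption and appears nowhere in the article. Even if this is the origin, a precision calculation does not deliver 80 % power for a comparison. The safe statement is that 2.14 does not reproduce the stated power.
- **Repeated rounds.** Three surveys follow baseline in the first phase. With a design effect of 2.14, the variance of an arm mean is scaled by (0.9525/600)(1 + 2r)/3 + (0.0475/24)(1 + 2s)/3, where r is the within-child and s the within-gott correlation between rounds. Assuming r from 0 to 0.4, power is about 65 to 72 % if s = 1 and about 76 to 84 % if s = 0.5. Stratifying by kebelle might help further. The true power of the full analysis could thus exceed 57 %, but the prevalence calculation takes no credit for any of this, and the correlations are assumed. The 57 % should be labelled single-round.
- **0.15 as variation in cluster size.** This would remove the clash between the two inputs, but gotts have a fixed 25 households, and power under 2.14 would still be about 56 %.
- **48 gotts per arm.** With 1,200 children per arm, power under 2.14 would be 85 %. The stated 600 per arm, 24 intervention gotts and 1200 households in total rule this out.
- **Only a reporting matter.** Enrolment and analysis do not change, which is true. The sentence is nonetheless the power claim for the primary endpoint.

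**Conclusion.** The point holds. The two clustering assumptions are incompatible at 25 children per gott (design effect 1.17 against 2.14, or coefficient of variation 0.15 against 0.39), and the design effect of 2.14 is incompatible with 80 % power at 600 per arm. Under 2.14 the single-round power for a 30 % reduction is about 57 % (56 to 57.5 % depending on the variance formula), and 80 % would need about 1,044 children per arm. Under 0.15 the printed size and power are correct, but the clustering allowance is much smaller than the reader is told. These figures assume two-sided 5 %; at one-sided 5 % the power under 2.14 is 68 %, still short of 80 %. The documents do not show which clustering value is the supported one, so only the authors can resolve it.

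**What to change.** State one clustering parameter for the prevalence endpoint, say whether it is a between-gott coefficient of variation or a design effect, and name the data behind it. State alpha and sidedness in the same place. Then:

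- if 0.15 is the value used and supported, replace 2.14 with about 1.17 and keep the 80 % claim;
- if 2.14 is the supported value, replace 0.15 with about 0.39 and give the single-round power for a 30 % reduction as about 57 %, with about 39 % as the reduction detectable at 80 % power. Any credit for repeated rounds should be added openly, with its assumed correlations.

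The choice should rest on evidence about clustering, not on which value preserves 80 %. The incidence section prints a k of 0.213422 from the preliminary survey. That describes rates rather than prevalence, so it does not transfer directly, but the authors should be ready to explain the difference.

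The cost is one corrected sentence. The 48 gotts and 1200 households stay as they are; the stated power may become less favourable.
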